#### Task acceptability

Participants are asked to self-administer the Endorsement and Discomfort Scale (EDS) [40] to rate the acceptability of the ABM training. Following the scoring method described by Milosevic, Levy, Alcolado, and Radomsky [41], a single score is calculated for the whole scale. The wording of the instructions and the questions addressing each item were adapted for this study based on advice from [name] (personal communication), the lead author of the manuscript which describes this scoring method.

### Intervention

Both the sham and ABM conditions involve 240 trials per session. We use an irrelevant-feature version of the modified AAT [14] (i.e. implicit training) which helps maintain participant blinding. Images are presented surrounded by a rectangular “frame” (i.e. a black rectangle surrounding the image) which is in either “portrait” or “landscape” orientation. Both conditions involve the same task instructions: participants are instructed to “push” the joystick in response to pictures with a landscape-oriented frame and “pull” in response to pictures with a portrait-oriented frame. Push and pull responses cause the image to shrink and expand, respectively, as previously detailed in the description of the AAT.

In the sham condition, 80 pictures (40 methamphetamine and 40 positive; i.e. all pictures except the 20 used solely for the AAT) are each presented in random order, three times per session. In the ABM condition, only the 10 of the 40 ABM pictures from each category that were most highly rated in the picture selection task (i.e. 20 pictures in total) are used, each presented 12 times. In the sham condition, methamphetamine-related images and positive images each comprise 50% of portrait-oriented images and 50% of landscape-oriented images, so that participants are not systematically trained to approach or avoid either type of image. In the ABM condition, 95% of the “push away” (i.e. landscape-oriented) trials are methamphetamine-related (and 5% positive) and 95% of the “pull” (portrait-oriented) trials are positive (and 5% methamphetamine-related), to systematically train participants to avoid methamphetamine-related images and approach positive images. The inclusion of 5% of trials where the content-orientation correspondence is reversed is intended to ensure that participants attend to task instructions (i.e. to make response decisions based on picture orientation, rather than content) and to improve the likelihood of participants being blind to condition in case participants from different conditions discuss the study with each other.

In both conditions, each session is preceded by a display of the task instructions, followed by 8 practise trials in which participants will respond to empty rectangles (4 in landscape and 4 in portrait orientation), to ensure they are familiar with the task instructions before commencing the training trials. During both practise and training trials, if participants make an incorrect response (i.e. move the joystick to its maximum extent in the incorrect direction), a red “X” is displayed and they are required to repeat that trial. The training task takes around 15 min to complete.

### Allocation

Randomisation occurs automatically at the time participants commence their first session of ABM. A randomisation sequence detailing which participant numbers are assigned to which condition is programmed into each laptop computer, using a blocked 1:1 allocation ratio. Since separate laptops are used for each recruitment site, randomisation is therefore stratified by site. Randomisation sequences were generated by the computer programmer responsible for programming the ABM tasks prior to commencing the study. The randomisation sequences are stored within a database on a password-protected server. The program’s access to these data is automated and manual access to the database is limited to the programmer, chief investigator, and a statistician not involved in data collection. A local copy of the randomisation sequence stored on the computer is encrypted to prevent accidental unblinding (i.e. to prevent staff involved in recruitment at sites from knowing what condition a participant will be assigned to prior to them commencing the first ABM session, and to prevent staff involved in conducting follow-ups from becoming unblinded to participant condition prior to assessing outcomes). When participants commence an ABM session, the researcher enters the participant’s number, and the ABM program queries the database (or the local copy, if there is no internet connection) to determine the condition associated with that number.

### Procedure

Clinicians responsible for admitting patients to the sites screen clients within the first week of their admission to rehabilitation. If a client is deemed eligible, the clinician informs them of the opportunity to participate in research and asks them if they are interested in discussing it with research staff. If the patient expresses interest, the clinician alerts the research team, and a research assistant then approaches the patient (approximately 1 week after admission to residential treatment) to provide a verbal and written explanation of the project and collect written informed consent if the client is willing to participate. A master version of the participant information sheet and consent form can be found on the Australian New Zealand Clinical Trials Registry (https://www.anzctr.org.au/Trial/Registration/TrialReview.aspx?id=378804&isReview=true) (Fig. 1).

**Fig. 1 Fig1:**
[figure not shown]
Participant flow through stages of the study

Following this, the researcher administers the interviewer-administered questionnaires (demographic/clinical history, SCID, TLFB). The researcher also collects contact details that can be used to contact the participant once they have discharged from residential treatment, including phone numbers, email and postal addresses, messaging app details, and contact details of others (e.g. friends, relatives, or clinicians) who can help pass messages onto the participant if we are otherwise unable to contact them. The participant then self-administers the SDS and CEQ. This is followed by the picture selection task and AAT, and then the first session of ABM. Due to the length of the recruitment process, questionnaires, and tests administered prior to commencing the first session, there is flexibility regarding whether these procedures are all done on the same day, or split into 2 separate sessions (e.g. baseline questionnaires in one session and session 1 in a separate later session, as shown in Table 1). Moreover, the first session of ABM is conducted at least 7 days after the participant commences residential treatment, to minimise the degree to which acute withdrawal symptoms (e.g. fatigue, emotional lability) interfere with engagement in the training task.

**Table 1 Tab1:** Schedule of measures and interventions

Expected times:	*1 week after admission to rehabilitation*	*1–3 weeks after admission to rehabilitation*			*4 weeks after leaving rehabilitation*	*12 weeks after leaving rehabilitation*
Time point:	*Baseline*	*Session 1*	*Sessions 2–5*	*Session 6*	*4-week follow-up*	*3-month follow-up*
*Eligibility screening*	X					
**Assessments:**						
*Demographic and clinical history*	X					
*SCID-5-RV*	X					X
*SDS*	X				X	X
*TLFB*	X				X	X
*CEQ*		X		X	X	X
*Picture selection*		X				
*AAT*		X		X		
*EDS*				X		
*Blinding check*						X
**Intervention:**						
*ABM—training*		X	X	X		

*AAT* approach-avoidance task, *ABM* approach bias modification, *CEQ* Craving Experience Questionnaire, *EDS* Endorsement and Discomfort Scale, *SCID-5-RV* Structured Clinical Interview for DSM-5 Disorders—Research Version, *SDS* Severity of Dependence Scale, *TLFB* timeline follow-back

ABM is repeated 3 times per week for 2 weeks, for a total of 6 sessions. There is flexibility regarding frequency of sessions to try to ensure that as many participants as possible complete 6 sessions prior to discharge. For example, if a session is missed due to participant illness, additional sessions can be scheduled after 2 weeks if 6 have not yet been completed at that point, or more than 3 sessions can be conducted in a week if the participant is not staying longer (or if their planned discharge is moved to an earlier date). However, only one session can be administered per day (i.e. multiple training sessions are not conducted on the same day).

Immediately before and after each ABM session, participants are asked to rate the intensity of their current methamphetamine craving on a single-item visual analogue scale (VAS). The VAS is presented with the question, “How strong is your craving for methamphetamine right now” displayed above it, and is anchored with the words “not at all” and “extreme” at the left and right ends of the scale, respectively. Ratings are recorded on a 0–100 scale. If a participant rates their craving in the right half of the VAS (i.e. closer to “extreme” than “not at all”) at any time, the researcher administering training checks if the participant feels comfortable continuing to participate, reminds them that they can withdraw at any time, and checks if they would like support from the rehabilitation facility’s clinical staff. The same steps are taken if a participant expressed distress at any time during their participation while they are staying at the rehabilitation facility. If they request support from clinical staff, the researcher will cease any study procedures and find a member of clinical staff. The intervention will be discontinued if the participant expresses a desire to withdraw from the research or if clinical staff at the recruitment site inform the researchers that the participant is no longer able to participate. If any participant expresses distress during their participation, this is reported to the trial coordinator to be recorded, regardless of whether or not it results in the participant withdrawing from the trial.

Following the final session of training, the AAT and CEQ are re-administered. Participants are also asked to complete the EDS to assess task acceptability. Participants are given a $60 supermarket gift card for completing training. Following their discharge from the site, a researcher obtains (de-identified) information from the site clinical records regarding the participant’s history of physical health and psychiatric diagnoses, substance use history, and medications administered to them during their residential stay.

One and 3 months following discharge from rehabilitation, a researcher not involved in administering training (and therefore blind to treatment condition) phones the participant and administers the TLFB, CEQ, and SDS. At the 3-month follow-up, the SCID-5-RV is also administered. We also assess continuous abstinence since discharge with a categorical (yes/no) question regarding any illicit amphetamine use since the previous follow-up and, if any has been used, the date of first use is assessed to allow survival analysis of time to first lapse. One-month follow-ups will occur no earlier than 28 days after discharge, and may be conducted up to 56 days post-discharge. Three-month follow-ups may be conducted no earlier than 84 days (i.e. 12 weeks) post-discharge and may be conducted up to 150 days post-discharge. Participants are sent a $20 supermarket gift card for each follow-up completed. At the 3-month follow-up, we also ask participants “Do you believe you received the form of training intended to reduce impulses to approach drugs or do you believe you were in the placebo group who received a form of training that was not designed to reduce approach impulses?” to assess blinding.

In accordance with intention-to-treat principles, we attempt to follow up all participants who are randomised (i.e. who commence the first session of ABM training), regardless of how many sessions they complete, unless they withdraw from participation. If a participant tells a researcher that they wish to withdraw (or if they tell clinical staff at the residential facility, and this is communicated to a member of research staff) the researcher seeks to ascertain their reason for withdrawal and communicates this to the study coordinator, so that the reason for withdrawal can be recorded. Reasons for withdrawal are classified according to whether they are related to the acceptability of the study protocol (e.g. finding the ABM training or questionnaires distressing) or are unrelated (e.g. the participant simply losing interest in participating, or facing stressors unrelated to study participation).

### Data management

Questionnaires are computerised and administered, using Qualtrics software, on the laptops used for training (except for the TLFB, as described below). Paper copies are available in case an internet connection is unavailable, and if questionnaire data is collected in this way, the researcher who collected the data inputs it into the Qualtrics database at the soonest available opportunity. The TLFB is administered on paper, and the variables to be derived from it are then entered into Qualtrics by researchers experienced in conducting and interpreting TLFB interviews. All TLFB data are subject to double-entry (i.e. entered by two separate researchers into 2 separate Qualtrics pages). At the conclusion of the study, these two entries will be examined for discrepancies, which will be corrected to produce a final version of the methamphetamine use data. Upon completion of the computerised tasks (i.e. picture selection, AAT, and ABM), response/performance data files will be sent to the trial coordinator for storage on a shared drive in a folder accessible only to the researchers involved in this study. The researcher on site will also save a local text file on the laptop used to administer these measures/tasks.

All Qualtrics entries, paper questionnaires, and computer task data files are labelled only with the participant’s number, not their name or other identifying details. The only form on which the participant number is listed alongside their name and contact details is the locator form, which is stored in a locked filing cabinet separate to where other paper data is stored, and the computer file containing these details is protected with a unique password shared only with the chief investigator and those staff responsible for conducting follow-ups. Once data collection and cleaning is complete, all data stored on Qualtrics will be downloaded into files to be stored in the project folder on a password protected drive and will be deleted from Qualtrics. The final dataset will be under the custodianship of the chief investigator, and access to it is limited to the investigators and trial staff approved by the primary ethics committee to be part of this trial.

### Outcomes and statistical methods

#### Primary outcome

The primary outcome is past-month abstinence from methamphetamine, as measured by the TLFB at each follow-up. The 3-month follow-up is the primary end-point for this outcome, and the 1-month follow-up will also be analysed as a secondary end-point. At each end-point, this outcome will be tested by comparing the proportion of participants reporting past-month abstinence using Pearson’s chi-square tests.

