### Study setting

We will conduct this trial at 3 services which offer 4-week residential addiction rehabilitation programmes. In these programmes, clients’ withdrawal symptoms are medically managed (typically during the first week of withdrawal) and clients participate in a range of group therapy activities. One site is a public substance use withdrawal management and stabilisation service attached to a large public hospital. Another site is a private psychiatric hospital which offers an addiction treatment programme. The third site is a standalone private addiction rehabilitation hospital. All sites are located in the Melbourne metropolitan area, Australia.

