### Sample size

We aim to recruit 100 participants. This trial is partly intended to establish effect size estimates for future larger trials, and the projected sample size for this trial is not based on an a priori power calculation. This will be the first randomised controlled trial (RCT) of ABM in a MUD sample; hence, there is little basis to estimate an expected effect size. The sample size was therefore pragmatically based on an estimate of the number of participants that could realistically be recruited from the participating sites within the available recruitment period. Across the 3 recruitment sites, an average of approximately 9 MUD clients are admitted each week. In our pilot study [33], we found that approximately two thirds of MUD clients met eligibility criteria, and approximately half of those who were eligible (i.e. approximately one third of all MUD admissions) agreed to participate. As such, we anticipate that we will recruit an average of 3 participants per week across the 3 sites, allowing a sample of 100 to be recruited in approximately 8 months. To ensure that opportunities for recruitment are not missed, the project manager liaises with intake staff on a weekly basis in order to check that they have screened every admission for eligibility, so that all clients entering treatment at the study sites and meeting eligibility criteria can be approached for recruitment.

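### The abstinence analyses leave out the site strata and baseline use; the chi-square is valid but gives up a modest amount of power

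*Protocol article*

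**What the plan says.** In the Protocol article, under Primary outcome, past-month abstinence is measured by timeline follow-back (TLFB): "The 3-month follow-up is the primary end-point for this outcome", the 1-month visit is a secondary end-point, and at each "this outcome will be tested by comparing the proportion of participants reporting past-month abstinence using Pearson’s chi-square tests". Under Secondary outcomes, continuous abstinence since discharge is also compared by a Pearson chi-square, and time to first lapse by a Cox regression between groups. No site term or baseline covariate is named for any of these. The only logistic models for abstinence are exploratory ones for moderation by impulsivity, and they name no site or baseline-use term either.

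Under Allocation: "Since separate laptops are used for each recruitment site, randomisation is therefore stratified by site". Under Study setting, the three sites are different kinds of service: "One site is a public substance use withdrawal management and stabilisation service attached to a large public hospital", the second is a private psychiatric hospital and the third a private addiction hospital. Under Substance use, the TLFB at baseline covers the 28 days before residential treatment.

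Under Sample size: "This trial is partly intended to establish effect size estimates for future larger trials". The target of 100 was set by expected recruitment, with no power calculation behind it.

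**The concern.** The design uses site to form the randomisation strata and the analysis then sets it aside. If abstinence differs between sites, stratified allocation balances that difference across the arms, but an unadjusted test still counts it as random error. The test then rejects slightly less often than its nominal level, and power is lost. Baseline use, which may also predict outcome, is collected and left unused.

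This is a matter of efficiency in a trial with little power to spare. It also bears on reporting. The trial is meant to inform the effect size for later trials, and an analysis that respects the strata and reports a risk difference with its interval serves that aim better than a test alone.

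**Working it through.** **The plan's own figure.** The protocol's only sample-size arithmetic is about feasibility: 9 admissions a week × 2/3 eligible × 1/2 consenting = 3 a week; 100 / 3 = 33.3 weeks, and 33.3 / 4.345 = 7.7 months. This agrees with the stated 8 months or so. There is no power figure to reproduce.

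**Inputs from the documents.** 100 participants, 1:1, blocked within three sites. Sham abstinence about 1 − 0.47 = 0.53, from the treatment outcome study cited in Background. This is a proxy, since it counts any use within 3 months of starting rehabilitation. Pilot 3-month retention 55% (Discussion).

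**Assumptions.** Two-sided 5% level; 73% abstinent on active training (a 20-point difference, for illustration); blocks of 4; and all prognostic strengths. The protocol states none of these.

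**Unadjusted power.** For 53% v 73%: 54.5% with 50 per arm and 33.2% with 27.5 per arm.

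**Why ignoring the strata is conservative.** Assume equal-sized sites with abstinence 35%, 55% and 75%.
- Within-site variance: (0.35×0.65 + 0.55×0.45 + 0.75×0.25)/3 = 0.2208.
- Total variance: 0.55×0.45 = 0.2475.
- Ratio: 0.892. The effective critical value is 1.96/√0.892 = 2.075, so the true size is about 3.8% under perfect balance.
- With sites at 45%, 55% and 65%: 0.2408/0.2475 = 0.973, and the true size is about 4.7%.

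**Simulation A: wide site spread (35/55/75% in sham, log odds ratio 0.9; 6,000 trials per cell).** With 100 followed, the chi-square has size 4.5% and power 49%; the Cochran-Mantel-Haenszel (CMH) test by site has 5.2% and 52%. At 55% follow-up, power is 29% v 31%. With a baseline predictor added (log odds ratio 0.8 per SD, treatment effect 1.0; 2,500 trials) and 100 followed, power is 54% for the chi-square and 62% for the logistic likelihood-ratio test (size 4.5% v 5.1%).

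**Simulation B: 53% v 73% throughout, site shares 40/35/25%, 3,000 trials per row.** The logistic model contains site and one baseline covariate. Power in %:

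| Analysed | Site step / covariate per SD (log-odds) | Chi-square | CMH by site | Logistic |
|---|---|---|---|---|
| 100 | 0 / 0 | 56.0 | 55.7 | 56.7 |
| 100 | 0.3 / 0.3 | 54.2 | 54.4 | 56.5 |
| 100 | 0.5 / 0.5 | 55.7 | 56.6 | 60.3 |
| 100 | 0.8 / 1.0 | 54.1 | 56.3 | 65.8 |
| 80 | 0.5 / 0.5 | 47.0 | 47.6 | 51.7 |
| 55 | 0.5 / 0.5 | 34.7 | 35.1 | 38.7 |
| 55 | 0.8 / 1.0 | 35.0 | 35.2 | 45.3 |

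Monte Carlo error on each power is about 1 point.
- At 100 analysed, the gain from site alone runs from nil to about 2 points.
- At 100 analysed, the gain from site plus covariate runs from 56.7 − 56.0 = 0.7 to 65.8 − 54.1 = 11.7 points.
- The moderate row at 100 gains 60.3 − 55.7 = 4.6 points, but the simulated sizes there were 6.1% (logistic) and 5.4% (chi-square). Roughly 4 is therefore a fair reading, and a generous one.

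**Near 55 analysed.** The likelihood-ratio test becomes liberal. In Simulation A its size was 6.5%; a raw gain from 31% to 38% shrank to about 1 point once calibrated. In the last row of Simulation B its size was 6.8% against 5.5% for the chi-square, so part of that 10-point difference is also excess size; that row was not recalibrated.

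**Validity.** Across all null scenarios in Simulation B the chi-square rejected 4.3% to 6.5% of the time. Discreteness and simulation noise at these sample sizes are as large as the conservatism itself.

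**Precision of the crude difference.** 1.96 × √(0.53×0.47/n + 0.73×0.27/n) gives a 95% half-width of about 19 points at n = 50 per arm and 25 points at n = 27.5.

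**The case against.** The strongest reply is that a two-proportion test is transparent and valid, and that the gain from adjustment is small and undocumented. No passage gives site-specific abstinence, and all three services run 4-week residential programmes with managed withdrawal and group therapy, so a 40-point spread between sites is an assumption. Nor does any passage say that pre-admission use predicts abstinence after discharge. Low numbers and loss to follow-up matter more. All of that stands, and it limits the size of the point. It does not remove the point: the unadjusted test is a stated choice, and using the strata costs essentially nothing even if they prove uninformative.

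Three stronger readings are tempting, and the documents support none of them.
- A reader might infer that the chi-square is invalid. The error rates above show otherwise.
- A reader might infer that chance imbalance in site or baseline use after dropout biases the result. Chance imbalance is already covered by the test's error rate. Dropout that differs by arm would be a separate problem, which site adjustment does not settle.
- A reader might infer that the plan yields no effect estimate and so defeats its own estimation aim. The two proportions being compared give a crude risk difference and interval directly, and the form of reporting may stand in an analysis plan that is not shown.

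**Conclusion.** The point holds as one of efficiency. The primary and continuous-abstinence analyses leave out the randomisation strata and a baseline measure already in hand. The cost is about 0 to 3 points of power for site alone. For site plus baseline use it is about 1 to 12 points with 100 analysed, roughly 4 under moderate prognostic strength, and little after calibration near 55. These ranges depend on assumed site differences, covariate strength and treatment effect; the protocol itself says "there is little basis to estimate an expected effect size". The change is worth making because it is nearly free, but it will not rescue a trial whose unadjusted power for a 20-point difference is about 55% at best.

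**What to change.** By dated amendment, made before any unblinded analysis, choose one of the following as the primary analysis of past-month abstinence at 3 months:

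- a comparison stratified by site: CMH test, with a Mantel-Haenszel risk difference and 95% confidence interval; or
- one logistic model with group, site and baseline TLFB days of use, reported as a standardised risk difference with 95% confidence interval.

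Fix the estimator now. It should not switch to another method according to how many participants are followed up. If the logistic model is chosen, its small-sample error rate should be checked at about 55 analysed before it is adopted. Use the same adjustment for 1-month and continuous abstinence, stratify the Cox model by site, and keep the Pearson chi-square as a supportive analysis. The reported interval then also serves the effect-size aim under Sample size.

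The cost is wording and an amendment; no new data are needed. Timing matters, because recruitment began in March 2020 and the protocol permits interim analyses, seen by the chief investigator, for reports due before completion. The amendment should record whether any such analysis has already been run, so that the choice of adjustment cannot be taken as driven by the data.
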